# 1. INTRODUCTION

## 1.1 Background

Dementia is a leading cause of mental and physical disability in the elderly. Vascular dementia (VaD), which accounts for 15-20% of all dementia cases, is a syndrome of acquired cognitive functional impairment with a complex pathophysiological basis. Viable pharmaceutical options for VaD are currently lacking. The conventional VaD drug regimen has tended to focus on single therapeutic targets such as cholinesterase (ChE) or glutamate receptors and does not appear able to address the complex and multi-system nature of VaD.

Combination therapies using multiple herbs are common in Chinese medicine. These complex chemical mixtures are believed to be able to enhance therapeutic efficacy through synergistic and multi-target mechanisms and are ideal for disorders such as VaD that have multifactorial/multisystem pathophysiological components. Based on this theory, our team have employed conventional pharmaceutical techniques to develop a novel, standardised herbal formulation, Sailuotong (*SLT*) targeting VaD. Data from the preclinical studies have shown significant improvements in memory functions and in pathogenic biochemical parameters in various animal dementia models. Appropriate safety of *SLT* has been shown in the acute and chronic toxicity and herb-drug interaction studies. A pilot clinical trial of a 4-month *SLT* treatment has demonstrated a significant improvement in cognitive function in patients with VaD. A larger scale clinical trial with a longer intervention period and greater statistical power is needed to confirm the efficacy and safety of this novel formulation for VaD.

Building on these encouraging results, we propose to undertake a rigorous phase III clinical trial in 238 mild to moderate VaD patients to evaluate the clinical efficacy of *SLT* treatment over a 52-week period. Cognitive and functional improvement, global assessment of change, quality of life and safety will be assessed regularly over a period of the intervention (52 weeks) and follow-up (13 weeks).

This project is innovative and will provide vital efficacy and safety data for this novel standardised formulation. Success in this project may lead to a breakthrough intervention for VaD. The project will help build complementary medicine research capacity through national and international collaborations.

## 1.2 Objectives

In this multicentre, randomised, double-blind, placebo controlled trial, we propose to evaluate the clinical effectiveness of *SLT* for the symptomatic improvement of VaD in 238 patients with mild to moderate probable VaD or Alzheimer's disease with cerebrovascular disease (AD+CVD). Specifically, the objectives of the study are to:

- determine the efficacy of the herbal intervention on cognitive function, activities of daily living, and quality of life, and
- monitor the safety of *SLT* as a treatment for VaD or AD+CVD during 52 weeks

We hypothesise that a 52 week treatment of *SLT* as compared with placebo will be clinically effective and well tolerated in participants with VaD or AD+CVD. The design of this study follows the European Medicines Agency's Guidelines on Medicinal Products for the Treatment of Alzheimer's Disease and Other Dementia.

## 1.3 Efficacy Endpoints

### Primary efficacy endpoints

The primary efficacy endpoint will be the difference between *SLT* and the placebo groups in the changes in Vascular Dementia Assessment Scale-cognitive Subscale (VaDAS-cog) and Alzheimer's disease Cooperative Study-activities of daily living (ADCS-ADL) scores from Baseline and 26-, and 52-week follow-up visits.

### Secondary efficacy endpoints

The secondary efficacy endpoints of the study will be the differences between the *SLT* and the placebo groups in the changes between baseline and 26-, and 52-week follow-up visits in:

- Scores of Clinician's Interview Based Impression of Change-plus (CIBIC-plus)
- Scores of additional executive function tests including CLOX and EXIT-25 from Baseline and 26-, and 52-week follow-up visits
- Scores of DEMQOL from Baseline and 26- and 52-week follow-up visits
- Scores of *Neuropsychiatric Inventory-Clinician rating scale* (NPI-C) from Baseline and 26- and 52-week follow-up visits
- Changes in MRI biomarkers from Baseline and the end of treatment assessment (52 week follow-up)

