#### 3.2 Sample

##### Sample Size

Following the release of the Phase II SLT trial results, sample size for this study was recalculated as the two studies used very similar participant cohorts and study design. In particular, the Phase II study provided useful data for VADAS-cog, one of the primary outcomes for the current study. Sample size was calculated using the Phase II trial outcome data for the two primary measures (VADAS-Cog and ADCS-ADLs). Based on their VADAS-Cog data, we expect the minimum between-group endpoint to be 3 or more units (with a standard deviation of 6.56) for a clinically meaningful change in cognition. Using a one-sided independent samples t-test for the purpose of calculating sample size, a total of 166 participants are required to detect this difference with 90% power at the 0.05 significance level. For the ADCS-ADLs, we anticipate the minimum between-group endpoint to be 3 or more units (with a standard deviation of 5.31) for a clinically meaningful change in daily functioning. Using a one-sided independent samples t-test for the purpose of calculating sample size with this measure, a total of 110 participants are required to detect this difference with 90% power at the 0.05 significance level. Allowing for a total non-compliance/withdrawal rate of 30%, 238 participants will be recruited into the trial across all centres to ensure 166 participants in the final analyses.

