### **Baseline visit (Week 0)**

Participants who meet all of the inclusion and none of the exclusion criteria will be scheduled to return to the site for their Baseline visit. At Baseline, the following will be performed:

- Check of inclusion and exclusion criteria.
- Check concomitant medications and procedures and note any changes in the CRF.
- Complete assessment scales VaDAS-cog, ADCS-ADL, CIBIC-plus, DEMQOL, NPI-C, CLOX and EXIT-25
- Complete MRI scans for substudy (50 participants only).

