### Secondary

- *Global Assessment of Change:* Clinician's Interview Based Impression of Change-plus (CIBIC-plus) is a reliable tool to rate participant's condition by a clinician experienced in the management of patients with dementia (global assessment). CIBIC-plus is a semi-structured interview and include four categories for evaluation – general, mental/cognitive state, behaviour and activities of daily living. It is estimated to take 30-45 min to complete.
- *Additional Executive Function Tests:* Small vessel disease that causes subcortical ischemic impairments, including lacunar infarcts and ischaemic white-matter lesions, is the most common type of vascular dementia in elderly people. Executive dysfunction, together with slowness of mental processing, early motor disturbances, and behavioural disorders are the main symptoms of vascular dementia. In this study, two additional instruments are employed for the further assessment of the executive function including CLOX and EXIT-25. Both instruments have been validated in various dementia cohorts including vascular dementia.

- CLOX: CLOX is a modified version of a clock drawing task and has been proven to be quick and sensitive tool for the assessment of executive function in elderly dementia patients. It has also been used a rapid method for dementia screening as it shows strong correlations with other traditional cognitive measures.
- EXIT-25: EXIT-25 was developed by the same group of researchers who developed CLOX with the aim to define the behavioural sequelae of executive cognitive dysfunction in dementia patients. It contains a 25-item interview scored from 0-50 and takes 15 minutes to complete. EXIT-25 correlates well with other executive control function tests such as Wisconsin Card Sorting Test.
- *Quality of Life Assessment:* DEMQOL is recognised as one of the best dementia-specific health-related quality of life (HRQOL) instruments for mild to moderate dementia (MMSE  $\geq 10$  is ideal for the target cohort in this study). DEMQOL has both self- (28-item DEMQOL) and proxy- rating (31-item DEMQOL-Proxy) components providing different but complementary perspectives on quality of life in dementia. DEMQOL also shows comparable psychometric properties to the best available dementia-specific measures.

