### **Primary efficacy analysis**

The primary analysis will be linear mixed models through which we will test for differences between treatment groups on each outcome over time, with adjustment for random variation between treatment centres, with and without adjustment for other potentially important predicts (e.g. compliance, age, gender, severity of VaD). Non-linear changes over time will be tested by a) fitting time as categorical variable and b) testing for quadratic and cubic effects. Results will be reported as regression coefficients (or odds ratios if categorical) and associated 95% confidence intervals.

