|-----|----------------------------------------------|--------------------------------|----------------------------------------------------------------------------------------------------------------------------------------------------------------------------------------------------------------------------------------------------------------------------------------------------------------------------------------------------------------------------------------------------------------------------------------------------------------------------------------------------------------------------------------------------------------------------------------------------------------------|----------------|-----------------------------------------------------------------------------------------------------------------------------------------------------------------------------------------------------------------------------------------------------------------------------------------------------------------------------------------------------------------------------------------------------------------------------------------------------------------------------------------------------------------------------------------------------------|
| 3.0 | Week 0, 26 and 52 visits (assessment visits) | Face-to-face on-site           | 
Part of the testing including VaDAS-cog, Exit-25, CLOX, CIBIS/CIBIC plus will be conducted as per Item 3.1.
 
Part of the testing including ADCS-ADL, DEMQOL, DEMQOL-Carer and NPI can be conducted remotely (i.e., over the phone) to reduce face-to-face contact time as per Item 3.2
                                                                                                                                                                                                                                                                                                                  | All Centres    | 
Centres will need to assess their current policies and procedures to determine appropriate action for these visits.
 
Researchers to obtain verbal consent to collect any data remotely and record this in the source visit notes.
                                                                                                                                                                                                                                                                                                            |

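### CIBIC-plus, a rating of change, is defined as a change from baseline and scheduled at Week 0; its baseline counterpart is never defined or tied to the endpoint

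*Protocol*

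**What the plan says.** **Endpoint.** Protocol section 1.3, Secondary efficacy endpoints, opens with a stem that covers the whole list: the difference between the SLT and "placebo groups in the changes between baseline and 26-, and 52-week follow-up visits in" the items that follow. The first item is "Scores of Clinician's Interview Based Impression of Change-plus (CIBIC-plus").

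**Schedule.** Section 3.3, Baseline visit (Week 0), instructs sites to "Complete assessment scales VaDAS-cog, ADCS-ADL, CIBIC-plus, DEMQOL, NPI-C, CLOX and EXIT-25". Table 1 marks CIBIC-plus at Weeks 0, 26, 52 and 65.

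**Instrument.** Section 5.1 places CIBIC-plus under a heading for global assessment of change and says it "is a reliable tool to rate participant's condition by a clinician experienced in the management of patients with dementia (global assessment"). It gives no score range, no anchors and no baseline form.

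**Baseline counterpart.** The only trace is in Appendix 4. Item 3.0, on the Week 0, 26 and 52 visits, says "Part of the testing including VaDAS-cog, Exit-25, CLOX, CIBIS/CIBIC plus will be conducted as per Item 3.1", and item 3.1 repeats the pairing. Item 4.0, on Week 65, names CIBIC alone. CIBIS is not defined anywhere.

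**Analysis.** Section 5.2, Primary efficacy analysis, uses linear mixed models to "test for differences between treatment groups on each outcome over time", with time also fitted as categorical and with quadratic and cubic terms. CIBIC-plus is not treated separately. Section 5.2, Missing data and protocol violations, fills missing items in the ITT analysis by last value carried forward, again with no exception.

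**The concern.** A rating of change already contains the comparison with baseline. The protocol asks for its change from baseline and provides a Week 0 value under the same name. Whatever is recorded at Week 0 cannot be a change rating. It is either a constant or a rating of something else, such as severity at entry.

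If it is something else, the text allows three faulty uses:

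- subtracting it from the Week 26 and Week 52 ratings;
- entering it as the time-0 response in a mixed model, so that two different quantities lie on one trajectory;
- carrying it forward as a change rating for a participant who leaves before Week 26 with no later assessment.

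CIBIC-plus is the only clinician global measure in the trial. The literature review uses the same measure to qualify the cognitive gains reported for galantamine and memantine, so readers will look to it to judge whether a VaDAS-cog gain is clinically visible. The definition should be unambiguous before unblinding.

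**Working it through.** **1. The plan's own figures, and whether they depend on this point.** For VaDAS-cog, section 3.2 says "we expect the minimum between-group endpoint to be 3 or more units (with a standard deviation of 6.56") and "a total of 166 participants are required to detect this difference with 90% power at the 0.05 significance level", using a one-sided t-test. The normal approximation per arm is 2 × (1.645 + 1.282)² × 6.56² / 3² = 81.9, rounded up to 82, or 164 in total. The exact one-sided t-test gives 83 per arm, 166 in total, as stated. For ADCS-ADL (3 units, SD 5.31), the approximation gives 53.7, rounded up to 54, or 108 in total; the exact t-test gives 110, as stated. Allowing for 30% loss, 166 / 0.70 = 237.1, rounded up to 238. All figures reproduce and none uses CIBIC-plus.

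**2. The passages side by side.** The stem in 1.3 requires a value at baseline and a value at follow-up. The Week 0 visit and Table 1 supply a baseline value labelled CIBIC-plus. The name and the 5.1 heading say that the instrument rates change. These statements fit together only if the Week 0 entry is a different instrument or a constant, and neither the endpoint, the schedule nor the instrument description says so. Appendix 4 names a pair of instruments for Weeks 0, 26 and 52 together, without saying which belongs to which visit.

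**3. What subtraction would do.** Let C be the later change rating and S the Week 0 entry, with SDs σ and s and correlation ρ.

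- Expected between-arm difference: E(C − S) differs between arms by the same amount as E(C), because randomisation equalises S in expectation.
- Variance: Var(C − S) = σ² + s² − 2ρσs.
- If S is constant, s = 0 and nothing changes.

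The protocol gives no CIBIC-plus SD, expected difference or correlation. The following values are therefore assumed: σ = 1.0, true difference 0.4, 83 per arm, two-sided 5%. The SE is √(variance × 2/83), and power is approximately Φ(0.4/SE − 1.96). Without subtraction, SE = √(2/83) = 0.155 and power is 73.1%. With subtraction:

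| s | ρ = 0 | ρ = 0.3 | ρ = 0.5 |
|---|---|---|---|
| 0.50 | variance 1.25, power 63.5% | 0.95, 75.3% | 0.75, 84.5% |
| 0.75 | 1.56, 54.0% | 1.11, 68.5% | 0.81, 81.6% |
| 1.00 | 2.00, 44.5% | 1.40, 58.6% | 1.00, 73.1% |

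Power falls only where s exceeds 2ρ (with σ = 1). A negative correlation would make the loss larger.

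A simulation of 20,000 trials (s = 0.75, ρ = 0, true difference −0.40) gave a mean of −0.400 with SE 0.154 for the rating alone, −0.401 with SE 0.193 after subtracting S, and −0.400 with SE 0.154 after subtracting a constant.

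**4. What carry-forward would do.** Assume a 1–7 scale with 4 meaning no change, no true effect, mean entry severity 3 to 3.5 recorded at Week 0, and loss before Week 26 of 15% in one arm and 25% in the other. After subtraction, participants with a carried-forward value score 0 and the others average 4 minus severity. The arm means differ by (0.85 − 0.75) × (4 − severity), which is 0.10 at severity 3 and 0.05 at severity 3.5. Here the protection from randomisation no longer holds, but the effect is small and needs unequal early loss.

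**The case against.** The strongest reply is that no subtraction is prescribed. A Week 26 rating of change since baseline is itself a change between those visits. The CIBIC-plus item is also the only one in the list that does not repeat the reference to baseline in its own line. The mixed model is not specified on difference scores, and whether a Week 0 value enters it is detail for the statistical analysis plan, which is not at hand. A baseline interview is needed as the reference for later ratings, so holding one at Week 0 is right and only its label is short. Appendix 4 suggests that the team used a counterpart.

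Much of this stands. The benign reading is possible, and a baseline counterpart was probably intended. But that reading does not explain why the Week 0 entry carries the name of the change rating. Nor does it keep that entry out of a model over time or out of carry-forward, since both rules apply without exception. The endpoint and the schedule are stated in the protocol itself, so this is a misstatement rather than a missing detail.

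A reader might also infer that the endpoint has no valid meaning, or that a chance imbalance in entry severity becomes a false treatment effect. The documents do not support either. With complete data the between-arm contrast is unbiased in expectation, and chance imbalance is already counted in the standard error. Nor do they support stating as fact that the Week 0 entry is a severity rating, since CIBIS is undefined. Calling CIBIC-plus the main endpoint would also be wrong: it is one of several secondary endpoints.

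Finally, early loss with only a Week 0 value may be uncommon. Withdrawing participants are encouraged to continue data collection and are asked to attend the end-of-treatment visit within 14 days.

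**Conclusion.** The point holds as a definition and labelling error of moderate severity; it is not one that must be fixed before the trial can be relied on. The protocol defines a change rating as a change from baseline, schedules it where it cannot be given, and leaves the probable baseline counterpart undefined and unconnected to the endpoint.

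If the text is followed literally and Week 0 holds a different kind of rating, the individual score cannot be interpreted. The randomised comparison stays unbiased in expectation with complete data. The effect on precision ranges from none, or even a gain, to a substantial loss: 44.5% to 84.5% power against 73.1% in the illustration. Those figures rest wholly on assumed SDs, difference and correlation and show a range, not a forecast. A constant Week 0 entry makes the effect nil. Bias arises only if a Week 0 rating of a different kind is carried forward and early loss differs between arms; it is 0.05 to 0.10 points under the assumptions shown.

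The finding that the passages conflict does not depend on any of these numbers. VaDAS-cog, ADCS-ADL and the 166 and 238 sample sizes are untouched.

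**What to change.** - **Section 1.3:** take CIBIC-plus out of the change-from-baseline stem. Define the endpoint as the CIBIC-plus rating itself at Weeks 26 and 52, made against the baseline interview. State that no baseline value is subtracted, entered as a time-0 response, or carried forward as a change rating.
- **Section 3.3, Baseline visit, and Table 1:** relabel the Week 0 entry as the baseline reference interview, the CIBIS named in Appendix 4.
- **Section 5.1:** define that interview and give the CIBIC-plus scale and anchors.

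An ordinal analysis, and use of the baseline interview as a covariate, are reasonable options but not needed to resolve the point.

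The cost is protocol wording and an eCRF label. No visit, assessment or participant is added, and the sample size does not change.

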## Safety endpoints

- Number of Adverse events and serious adverse events will be monitored during the course of the study.
- Changes in liver, renal, coagulation will be monitored during the course of the study.

## **2. Literature Review**

### **2.1 Vascular Dementia**

Dementia is a leading cause of mental and physical disability in the elderly and carries the highest disability weighting of all illnesses. VaD is a clinical syndrome of acquired intellectual and functional impairment that results from cerebrovascular and cardiovascular diseases and is the second most common cause of dementia after Alzheimer's disease (AD), accounting for 15-20% of all cases in western countries. The prevalence of VaD is between 1 and 4% in individuals over the age of 65 years. This figure is doubled every 5 to 10 years and for individuals over the age of 85, the prevalence of VaD surpasses that of AD. In Australia, there were around 245,400 dementia patients (~37,000 VaD patients) in 2009 and this figure is estimated to reach 1.13 million (~170,000 VaD patients) by 2050. In Asia and some developing countries, the prevalence of VaD is even higher, equaling or exceeding that of AD. VaD significantly impacts on life quality of patients and imposes a huge financial burden on the community and health care system. The total cost of dementia (including VaD) to the Australian health system was estimated at \$6.6 billion in 2002, representing 1% GDP and it may exceed 3% of GDP by 2050. 'Ageing well, ageing productively' is a current national research priority and acknowledges the significant burden dementia imposes to the community and health care system.

Cognitive impairment is the primary symptom of VaD. VaD can also cause disturbance of mood and behaviour and reduce quality of life. The pathophysiology of VaD is complex. It incorporates interactions between vascular aetiologies (cerebrovascular disorders and vascular factors), changes in the brain (infarcts, white matter lesions, atrophy) and host factors (age, education). The final common aetiopathogenic pathway usually attributes to a hypoxic, hypoperfusive or occlusive process resulting in ischemic damage in various areas of the brain, with subsequent cognitive and memory function impairment.

Currently, effective pharmaceutical interventions for VaD are lacking; standard treatment largely focuses on symptomatic management and prevention of additional brain damage via recognition and control of risk factors such as hypertension and atherosclerosis. Several classes

of pharmaceutical agents are used for the symptomatic management of VaD, among which ChE inhibitors and glutamate receptor antagonists are suggested as producing the best clinical outcomes. The most commonly used ChE inhibitors include donepezil, galantamine, rivastigmine and memantine. In two randomised, double-blind, placebo control trials, donepezil demonstrated significant improvement in cognitive function, clinical global impression and activities of daily living in patients with probable or possible mild to moderate VaD. The latest Cochrane review of galantamine in VaD demonstrated contradictory results. One of the two studies included in the review showed that galantamine treatment did not produce significant improvement in ADAS-cog and CIBIC-plus in VaD, while the other study reported a significant improvement in ADAS-cog but not in CIBIC-plus. Rivastigmine is a dual ChE inhibitor, targeting both major forms of ChE - acetylcholinesterase and butyrylcholinesterase. The most recent Cochrane review did not identify any suitable trials to be included in the analysis. Several smaller scale studies however, indicated some beneficial effect of rivastigmine in VaD. However, these studies suffered from either low patient numbers or did not compare rivastigmine to a placebo. Memantine is a glutamate antagonist and is suggested to produce neuroprotective effects via blocking NMDA-type glutamate receptors. Two recent clinical trials of memantine in mild-to-moderate VaD demonstrated a small but statistically significant improvement in ADAS-cog. However, this result was not supported by a clinical impression of change measured by the CIBIC-Plus. In summary, the existing evidence to support efficacy of pharmaceutical agents in VaD is relatively weak and inconsistent. Moreover, the long-term benefits of these interventions in VaD have not been validated. As a result, none of these agents are currently indicated for VaD under the Australian Pharmaceutical Benefit Scheme but are licensed for VaD in the UK.

